### Randomization and blinding

2.5

The included participants will be divided into the treatment group and the control group randomly in a 1:1 ratio. SAS9.3 software will be used for generating random sequences by an independent researcher who will be not involved in the period of treatment and data analysis. The central randomization system (provided by the department of oncology, Shanxi Province Hospital of Traditional Chinese Medicine) will be used and for each center, the clinical investigators will log into the central system by telephone or internet for applying for the randomization number for a new included patient.

### Intervention measures

2.6

The basic intervention will be basic antitumor therapies including chemotherapy, radiotherapy, immunotherapy, and targeted therapy for CRC.

The control group will just use the basic intervention, and the treatment group will use basic intervention plus BTF provided by Shanxi Province Hospital of Traditional Chinese Medicine for 12 weeks.

All included participants will be supervised by an experienced oncologist during this RCT in each center.

### Outcomes

2.7

#### Primary outcomes

2.7.1

1.Quality of life of CRC patients: measured by the medical outcomes study item short from health survey (SF-36) which developed by the Medical Outcomes Study and Karnofsky score (KPS). SF-36 is involving 8 aspects including physical functioning, role-physical, bodily pain, general health, vitality, social functioning, role-emotional, and mental health;2.The time of occurrence of liver metastasis, the size of tumor, and the expression of tumor markers in the serum;3.The score of TCM symptom for the type of liver depression spleen deficiency.

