Traditional Chinese medicine (TCM) is characterized by simplicity, convenience, simplicity, and efficiency, which provides a new therapy pattern. According to a recent study, combined with Western medicine treatment or not, TCM therapies have shown efficacy for CRLM. It can not only assist the human body to restore *qi* and create surgical conditions for some CRLM patients, but also play an important role in reducing side effects from surgery, radiotherapy, and chemotherapy. Through the search of clinical and experimental studies on TCM treatment of CRLM in recent years, it is found that the treasure house of TCM has not been fully tapped in the treatment of CRLM, the research quality is low. To enrich the means of TCM treatment, it should seek more effective and more abundant methods of TCM treatment of CRLM.

Buzhong Tiangan Formula (BTF) is an experience formula in treating CRLM, which has been used for more than 20 years in our team, while there are lacking of evidence on its effective in delaying colorectal liver metastasis (liver depression spleen deficiency type). So, the purpose of this study is to verify the efficacy of BTF in preventing the occurrence of CRLM and to prolong the time phase of CRLM.

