### Statistical analysis

2.10

Data analysis setting will follow intent-to-treat (ITT) principles. Data will be statistically analyzed by SPSS 23.0 software. Chi-Squared test will be used for enumeration data, and mean ± standard will be used for measurement data. Drawing survival curves of overall survival, progression-free survival, and DFS will use Kaplan–Meier and the difference between the treatment group and control group will use log-rank. If possible, subgroups analysis will be carried out by the left or right colon, gene status, sex, and age. *P* < .05 will be considered a significant statistical difference.

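### Three unranked composite primary outcomes (13 or more measures if SF-36 domains count separately) share one P < .05 rule, and nothing says which result decides the trial

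*Protocol article*

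**What the plan says.** Section 2.7.1 of the protocol article lists three numbered primary outcomes:

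- Quality of life, by SF-36 and KPS. On the first instrument it says "SF-36 is involving 8 aspects including physical functioning, role-physical, bodily pain, general health, vitality, social functioning, role-emotional, and mental health". No summary score is named.
- "The time of occurrence of liver metastasis, the size of tumor, and the expression of tumor markers in the serum". The markers are plural and not named.
- The TCM symptom score for the liver depression, spleen deficiency type.

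They are not ranked, not made jointly necessary and not combined. The abstract's primary list is shorter: quality of life, time of liver metastasis and the TCM score, without tumour size or markers.

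Section 2.10 supplies one decision rule, that P below .05 "will be considered a significant statistical difference". It assigns Kaplan–Meier and log-rank to overall, progression-free and disease-free survival only. It names no between-group test for continuous scores.

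On the comparison itself, section 2.6 says "The control group will just use the basic intervention". Section 2.5 has blinding in its heading but describes none. The Introduction gives the purpose as to "verify the efficacy of BTF in preventing the occurrence of CRLM and to prolong the time phase of CRLM"; the Discussion adds patients' quality of life as a goal.

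**The concern.** As written, a significant result on any component of any primary outcome could be presented as the trial's primary success. The error rate attached to such a claim is then not 5%, and the document does not bound it. The result that carries the claim also need not concern liver metastasis, which is the purpose in the Introduction.

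The second strand is bias. Patients know whether they take BTF. SF-36 is self-reported, so it can move through expectation alone, yet it ranks equally with the occurrence of liver metastasis. What is at stake is what the trial may claim at the end, and that cannot be settled credibly once the scores have been seen.

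**Working it through.** **Plan's own figures.** The document states no familywise error rate. Its drop-out step reproduces: 60 / (1 − 0.20) = 75 per group (section 2.4). The bias check below uses the 60 evaluable.

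**Count of measures (section 2.7.1).** 8 SF-36 domains + KPS + time to liver metastasis + tumour size + at least one serum marker + TCM score = 8 + 1 + 1 + 1 + 1 + 1 = 13. On the reading kindest to the plan, each numbered outcome is one test, giving 3.

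**Assumptions.** Each measure is judged at 5%. Sidedness is not stated and two-sided is assumed. The correlation between test statistics is not given, so a range is shown, using equicorrelated normal statistics with no true effect on any measure.

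**Any false significant result.** Under independence the chance is 1 − 0.95^k:

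- k = 3: 1 − 0.95³ = 14.3%
- k = 13: 1 − 0.95¹³ = 48.7%

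**False results favouring BTF only.** Each test then has a 2.5% error, and the chance is 1 − 0.975^k:

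- k = 3: 1 − 0.975³ = 7.3%
- k = 13: 1 − 0.975¹³ = 28.0%

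Common correlation ρ lowers these (numerical integration for ρ > 0):

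| Tests | ρ | Either direction | Favouring BTF |
|---|---|---|---|
| 3 | 0 | 14.3% | 7.3% |
| 3 | 0.5 | 12.5% | 6.3% |
| 13 | 0 | 48.7% | 28.0% |
| 13 | 0.5 | 33.4% | 16.7% |
| 13 | 0.7 | 24.1% | 12.0% |

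The reference values for a single test are 5% and 2.5%.

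**Expectation bias on one self-reported score.** Assume a shift of d standard deviations with no real effect and n = 60 evaluable per arm. The chance of a significant result favouring BTF is Φ(d·√(n/2) − 1.96), with √30 = 5.477:

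- d = 0.2: Φ(1.095 − 1.96) = Φ(−0.865) = 19%
- d = 0.3: Φ(1.643 − 1.96) = Φ(−0.317) = 38%

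The shift is an assumption; the documents give no figure for it.

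**Effect of the remedies.** One designated primary at 5% has a 5% error. Three primaries at 0.05 / 3 = 0.0167 each give 1 − (1 − 0.0167)³ = 4.9% under independence. Bonferroni and Holm hold the error at or below 5% whatever the correlation.

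**The case against.** **The document numbers three outcomes, not 13, and does not say that each component is tested.** This stands in part. The sentence on eight aspects describes the SF-36 instrument, and section 2.10 names no test for continuous scores, so a reader who infers 13 planned tests goes beyond the text. But no summary score or single measure is named either, so nothing prevents that reading, and three tests already give 12.5% to 14.3%.

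**A reader might infer that a false success is likely.** Chance alone does not support that. No figure above passes one half, and in BTF's favour the error is about 6% to 7% for three tests and 12% to 28% for 13. The inflation is real, but it should be stated at that size.

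**A reader might infer that KPS and TCM raters are unblinded.** The document does not say so. Lack of a placebo unblinds patients; it does not establish who rates. The bias point is therefore confined to the self-reported SF-36.

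**The shorter list in the abstract may be abbreviation.** It names the leading element of each numbered outcome, so it is weak evidence of two different primary sets. It is still worth aligning.

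**Multiple primaries are legitimate, quality of life is also a stated goal, and an analysis plan not shown may adjust.** The first two stand, and they are why the fix offers an alternative with several primaries. On the third, details of adjustment can be left to an analysis plan. The unranked primary list and the flat threshold are choices made in this document, and the finding rests on those.

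**Conclusion.** The point holds as a badly fixed decision rule. Three composite primary outcomes are listed without rank, and one threshold applies without a definition of success. If each is judged at two-sided 5%, the chance of at least one false significant primary result is roughly two and a half to three times nominal on the three-test reading, and about five to ten times nominal if 13 measures are tested. Restricting to results that favour BTF leaves a similar or slightly larger inflation relative to 2.5%. These figures rest on assumed correlations and on the inference that every listed measure would be judged by the single rule. The 19% to 38% for a self-reported score comes in addition and depends wholly on the assumed shift of 0.2 to 0.3 SD.

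**What to change.** Before any outcome data are seen, choose one of two routes.

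1. Make time to liver metastasis the single primary outcome at two-sided 5%, in line with the Introduction. Add it to the Kaplan–Meier and log-rank outcomes in section 2.10, which now omits it, and say how death before liver metastasis is handled. Then test one pre-named SF-36 summary score, followed by the TCM score, in fixed sequence. Each is tested only if the one before it is significant.
2. Because the Discussion also makes quality of life a goal, keep three primaries with one named measure each. Control the error by Holm, or by Bonferroni at 0.0167 each. Time to liver metastasis still needs its analysis named.

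Under either route, report the remaining SF-36 domains, KPS, tumour size and markers with confidence intervals and no confirmatory claim. State that patients are not blinded and whether the KPS and TCM raters are. Use the same primary list in the abstract and the body.

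**Cost.** The change is to protocol, analysis plan and registry wording; it needs no extra patients or procedures. A quality-of-life or TCM result alone would no longer count as success at an unadjusted P < .05. Under route 1, a non-significant liver metastasis result closes the sequence. Power for liver metastasis is not established, because the 60 per group in section 2.4 is based on survival, a secondary outcome. The report should say so.

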#### Secondary outcomes

2.7.2

1.Overall survival, progression-free survival, or disease-free survival (DFS);2.Tumor microenvironment, measured by vascular endothelial growth factor receptor (VEGFR) and Th1/Th2 in the serum;3.Immune state of the patient, measured by subset of the class of T-cells in the serum.

### Safety evaluation

2.8

A special safety supervisor will record each adverse event during the whole period of this RCT in detail.

### Data management and quality control

2.9

Any changes to the protocol should be approved by the ethics committee of Shanxi Province Hospital of Traditional Chinese Medicine. All the data of patients will be recorded in case report form (CRF) by a trained researcher. All information on patients should not be shared without their permission.

### Statistical analysis

2.10

Data analysis setting will follow intent-to-treat (ITT) principles. Data will be statistically analyzed by SPSS 23.0 software. Chi-Squared test will be used for enumeration data, and mean ± standard will be used for measurement data. Drawing survival curves of overall survival, progression-free survival, and DFS will use Kaplan–Meier and the difference between the treatment group and control group will use log-rank. If possible, subgroups analysis will be carried out by the left or right colon, gene status, sex, and age. *P* < .05 will be considered a significant statistical difference.

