**Methods::**

This randomized controlled trial (RCT) will be carried out in 3 different hospitals in Shanxi Province planning to recruit 150 CRLM patients with the type of liver depression spleen deficiency. The control group will be treated by basic antitumor therapy and the treatment group will use BTF plus basic antitumor therapy. The primary outcomes will be quality of life of included patients, the time of occurrence of liver metastasis, the score of traditional Chinese medicine symptom for the type of liver depression spleen deficiency; and the secondary outcomes will include overall survival, progression-free survival, DFS, tumor microenvironment and immune state of the included patient. Safety evaluation will be recorded during the whole study. All data in this RCT will be analyzed by SPSS 23.0 software. This study has been approved by the Clinical Research Ethics Committee of Shanxi Province Hospital of Traditional Chinese medicine (2021Y-06016).

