### Study design

2.1

This is a prospective, multicenter randomized controlled trial (RCT) of BTD for delaying colorectal liver metastasis (liver depression spleen deficient type). Included patients are planned to be divided into 2 groups: the treatment group (received basic anti-tumor drugs plus BTD), and the control group (received basic antitumor drugs). The patients are planned to be followed ups for 2 years after 12-week treatments. The flow diagram is shown in Figure 1. This protocol followed the Standard Protocol Items: Recommendations for Interventional Trials (SPIRIT) (Fig. 1).

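### The named log-rank and chi-squared tests take no account of the three hospitals, which costs some efficiency if hospital is prognostic (minor)

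*Protocol article*

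**What the plan says.** The abstract states that the trial will be "carried out in 3 different hospitals in Shanxi Province". Section 2.5 has patients "divided into the treatment group and the control group randomly in a 1:1 ratio", and "for each center, the clinical investigators will log into the central system by telephone or internet for applying for the randomization number". It does not say whether the sequence is stratified or blocked by hospital.

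Section 2.6 describes background treatment as covering chemotherapy, radiotherapy, immunotherapy and targeted therapy, with an oncologist supervising in each centre.

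Section 2.10 fixes the comparisons. For overall, progression-free and disease-free survival, "the difference between the treatment group and control group will use log-rank". For other data, "Chi-Squared test will be used for enumeration data, and mean ± standard will be used for measurement data". The only further factors it names are for subgroups: "subgroups analysis will be carried out by the left or right colon, gene status, sex, and age". Hospital is not among them.

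**The concern.** Hospital is known for every patient when the randomisation number is requested, so using it in the analysis needs no new data. It is also a plausible source of variation, because background therapy spans four modalities and patients are supervised centre by centre. A test that leaves out a prognostic factor of this kind pays for it in one of two ways, depending on a fact that section 2.5 leaves open:

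- If allocation is stratified by hospital, the arms are balanced within hospital, but an unstratified test still counts between-hospital variation as noise. Its standard error is too large.
- If allocation is not stratified, the hospital mix can differ between arms by chance. The unstratified test allows for this, but with less power than a test that uses hospital.

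What is at stake is precision, in a trial planned with 60 evaluable patients per group.

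**Working it through.** **The plan's own figures.** The article gives no figure for hospital effects. On sample size, the drop-out step reproduces: 60/(1 − 0.20) = 75 per group. The 60 itself does not: 65% v 55% at two-sided 5% and 80% power needs 376 per group, and 60 per group gives about 20% power. That is a separate matter. It matters here only because there is little power to give away.

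**Inputs.** Three hospitals (abstract); 75 + 75 = 150 patients, 1:1 (2.4, 2.5); medians 17 and 14 months (2.4), so the hazard ratio is 14/17 = 0.824 under exponential survival; follow-up of 12 weeks plus 2 years, about 27 months (2.1). Assumed, because the article gives no value: equal hospitals of 50, the share ρ of outcome variance due to hospital, and the spread of hazards between hospitals. Two-sided 5% throughout.

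**Continuous score.** Take a true effect for which the hospital-adjusted test has 80% power, a standardised shift of 1.960 + 0.842 = 2.802.

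- Allocation not stratified, hospital omitted: power = Φ(2.802·√(1 − ρ) − 1.960). Type I error stays at 5% over repeated allocation.
- Allocation stratified, hospital omitted: power = Φ(2.802 − 1.960/√(1 − ρ)), and actual type I error = 2[1 − Φ(1.960/√(1 − ρ))].

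| ρ | Power, not stratified | Power, stratified | Type I error, stratified | Adjusted analysis: 60 per group acts like 60/(1 − ρ) |
|---|---|---|---|---|
| 0 | 80.0% | 80.0% | 0.050 | 60 |
| 0.05 | 78.0% | 78.5% | 0.044 | 63 |
| 0.10 | 75.7% | 76.9% | 0.039 | 67 |
| 0.20 | 70.7% | 72.9% | 0.028 | 75 |

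**Chance imbalance without stratification.** With independent 1:1 assignment and 50 patients in a hospital, the standard deviation of the treated share is √(0.25/50) = 7.1 percentage points, so the 95% range is about 36–64%. If the totals are held at 75:75 over the whole trial, the standard deviation shrinks by √(100/149) = 0.82 to about 5.8 points, and the range is about 39–61%.

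**Log-rank test.** The formulas above do not apply to it, so it was simulated: exponential survival, control median 14 months, censoring at 27 months, 4,000 runs per scenario. The standard error is about 0.6 points on power and 0.3 points on type I error. In the not-stratified case the overall totals were held at 75:75.

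| Relative hazards of the hospitals | Allocation | Power, plain | Power, hospital-stratified | Type I error, plain |
|---|---|---|---|---|
| 1 / 1 / 1 | stratified | 16.3% | 16.2% | 0.051 |
| 1 / 1 / 1 | not stratified | 16.8% | 16.6% | 0.048 |
| 0.75 / 1 / 1.33 | stratified | 15.5% | 16.2% | 0.048 |
| 0.75 / 1 / 1.33 | not stratified | 16.1% | 16.9% | 0.051 |
| 0.5 / 1 / 2 | stratified | 11.3% | 16.0% | 0.036 |
| 0.5 / 1 / 2 | not stratified | 13.6% | 16.7% | 0.054 |

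The plain test loses nothing when hospitals are alike, under 1 point at a moderate spread, and 3–5 points (16.7 − 13.6 = 3.1; 16.0 − 11.3 = 4.7) when hazards differ fourfold between extreme hospitals. These losses start from power of only 16–17%. Its type I error lies between 0.036 and 0.054, with no excess over 5% beyond simulation error. The chi-squared test was not simulated.

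**The case against.** The strongest objection is that this rests on silence. The article says log-rank and chi-squared; it does not say they are unstratified, and a condensed article commonly leaves strata and covariates to the full protocol or analysis plan. That has real weight and is the main reason for a low rating. It does not remove the point, because section 2.10 names the tests and lists the factors of interest without hospital, so a better choice than the tests as written can be put forward.

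Four stronger readings are tempting, and the article does not support them:

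- A reader might infer that patients are randomised hospital by hospital. Section 2.5 describes how sites obtain a number from one system, not stratification or separate lists.
- A reader might infer that every planned test, including that of the syndrome score, ignores hospital. For measurement data section 2.10 gives only a description and names no test. The quoted log-rank sentence concerns survival outcomes that section 2.7.2 lists as secondary.
- A reader might infer that each hospital has its own therapy mix, or that the syndrome score and KPS are rated locally. Both are plausible, but neither is stated.
- A reader might infer bias or false positives. Chance imbalance under unstratified allocation is covered by the unadjusted standard error, and under stratified allocation the unadjusted test errs on the cautious side.

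It is also fair to say that the 5–20% variance share has no source in the article. At zero, adjustment gains nothing.

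**Conclusion.** The point stands as a minor one about efficiency. If hospital is prognostic, tests that take no account of it are conservative under stratified allocation, and less powerful and open to chance imbalance under unstratified allocation. With hospital explaining 5–20% of the variance of a continuous score, power drops from 80% to 71–78% (not stratified) or 73–78.5% (stratified). These score figures show what is at stake once a test is chosen; they do not show a fault in a test already named. For the log-rank test at the protocol's medians the loss is about 0–5 points, appreciable only if hospital hazards differ widely. All sizes rest on the assumed variance shares, hazard spreads and equal hospitals. The validity of the comparison is not in doubt on this ground, and adjusting for hospital would not repair the low power of the trial.

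**What to change.** In section 2.10, use a log-rank test stratified by hospital and a Cochran–Mantel–Haenszel test stratified by hospital in place of the unstratified tests. When the analysis of continuous scores is specified, include hospital as a factor with three levels.

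In section 2.5, state whether allocation is stratified by hospital. If recruitment has not started, have the central system allocate 1:1 within each hospital in blocks of randomly varying size. If it has started, leave the allocation as it is and change only the analysis, before outcomes are compared by arm.

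The cost is a few lines of text and, at most, one setting in the randomisation system; the requesting hospital is known there. The downside is a slight loss of efficiency if hospitals do not differ: in the simulation, 16.2% v 16.3% and 16.6% v 16.8% power, within simulation error.

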## Discussions

3

In recent years, the incidence and mortality rate of CRC is rising sharply in China. CRLM has been threatening the patients without efficacy treatment with western medicine, so the important thing that needs to solve is prevention. Chinese herbal medicine has been proved that no matter herbal decoction, tablet, or patent, the herbal medicine treating CRLM is mainly based on invigorating the spleen and invigorating *qi*, combining with soothing the liver and removing blood stasis, which reflects the overall idea of TCM in treating tumors and the theory of nourishing and dispelling pathogens. And this emphasized that the treatment of metastatic tumors should be divided into general and local treatment, and that systemic treatment should be put in the first place, and local treatment is on the basis of systemic treatment.^[14]^

BTF is a formula proved by [name], a famous Chinese doctor in China and composed of 15 herbals including *Huangqi, Baizhu, Shengma, Chaihu, Danggui, Huangqin, Baishao, Nvzhenzi, Wuweizi, Banzhilian, Biejia, Bayuezha, Xiakucao, Dangshen, Gancao* for treating CRLM (liver depression spleen deficiency type). [name] established the therapeutic principles of harmonizing liver and spleen, reducing toxin, and eliminating disease under the guidance of the harmony method. According to the concept of “Fuzheng does not stay evil, Quxie does not hurt positive,” the herbals to nourish spleen and liver and detoxify anticancer products are used, which will ensure the patient's *qi* and blood, viscera and body in harmony, eventually pursuit the state. Only when *Yin* is at peace and Yang is compact can essence-spirit be normal to achieve the condition of “human-tumor coexistence.”^[15]^

The results from this RCT will contribute to clinical practice by BTF for delaying colorectal liver metastasis (liver depression spleen deficient type). Our goal in this RCT will be to accomplish an RCT with high quality that utilizes validated evaluation measures not only for delaying the occurrence of liver metastasis itself but also focusing on the quality of life of patients and also will explore the possible therapeutic mechanisms. And the results from this RCT will be published in a relevant journal after finished.
